## Abstract

**Background:**

Mild traumatic brain injury (mTBI) affects ~18,000 military personnel each year, and although most will recover in 3–4 weeks, many experience persisting symptoms and impairment lasting months or longer. Current standard of care for U.S. military personnel with complex mTBI involves initial (<48 h) prescribed rest, followed by behavioral (e.g., physical activity, sleep regulation, stress reduction, hydration, nutrition), and symptom-guided management. There is growing agreement that mTBI involves different clinical profiles or subtypes that require a comprehensive multidomain evaluation and adjudication process, as well as a targeted approach to treatment. However, there is a lack of research examining the effectiveness of this approach to assessing and treating mTBI. This multisite randomized controlled trial (RCT) will determine the effectiveness of a targeted multidomain (T-MD) intervention (anxiety/mood, cognitive, migraine, ocular, vestibular; and sleep, autonomic) compared to usual care (behavioral management) in military-aged civilians with complex mTBI.

**Methods:**

This study employs a single-blinded, two-group repeated measures design. The RCT will enroll up to 250 military-aged civilians (18-49 yrs) with a diagnosed complex mTBI within 8 days to 6 months of injury from two concussion specialty clinics. The two study arms are a T-MD intervention and a usual care, behavioral management control group. All participants will complete a comprehensive, multidomain clinical evaluation at their first clinical visit. Information gathered from this evaluation will be used to adjudicate mTBI clinical profiles. Participants will then be randomized to either the 4-week T-MD or control arm. The T-MD group will receive targeted interventions that correspond to the patient’s clinical profile (s) and the control group will receive behavioral management strategies. Primary outcomes for this study are changes from enrollment to post-intervention on the Neurobehavioral Symptom Inventory (NSI), Patient Global Impression of Change (PGIC), and functional near-infrared spectroscopy (fNIRS). Time to return to activity (RTA), and healthcare utilization costs will also be assessed.

**Discussion:**

Study findings may inform a more effective approach to treat complex mTBI in military personnel and civilians, reduce morbidity, and accelerate safe return-to-duty/activity.

**Ethics and dissemination:**

The study is approved by the University of Pittsburgh Institutional Review board and registered at clinicaltrials.gov. Dissemination plans include peer-reviewed publications and presentations at professional meetings.

**Clinical Trial Registration::**

www.clinicaltrials.gov, identifier: NCT04549532.

## Introduction

1.

Mild traumatic brain injury (mTBI) affects ~18,000 military personnel each year (1). Although most military personnel with mTBI will recover in 3–4 weeks, many experience symptoms and impairments lasting months or longer, resulting in limited operational capabilities and duty restrictions (2). These “complex” mTBIs may involve vestibular, cognitive, somatosensory, and/or autonomic dysregulation that if left untreated can become chronic in affected personnel (3). This protracted course of recovery adversely affects the health of military personnel, results in productivity losses, and negatively impacts force readiness. In addition, mTBI places a significant burden on the Military Health System. The estimated one-year direct costs for mTBI-related care range up to $30,000 per military personnel (4).

There is growing agreement that mTBI is a heterogeneous injury involving multiple domains of symptoms and impairment (5–7). Research indicates that mTBI may involve different clinical profiles or subtypes that require a comprehensive multidomain evaluation and targeted approach to treatment (8, 9). Each of these clinical profiles is characterized by specific symptoms and impairment that can be targeted with matched treatments. Importantly, complex mTBI typically involves multiple, often overlapping affected domains including but not limited to anxiety/mood, cognitive, migraine/headache, ocular, sleep, vestibular, and autonomic (7, 9). Previous trials have failed to address this heterogeneity in their design, evaluation of clinical outcomes, and application of treatments.

Current standard of care for U.S. military personnel with mTBI involves initial prescribed rest, followed by primary care-based behavioral management (e.g., sleep regulation, stress reduction, hydration, nutrition), and symptom-guided management. Growing evidence suggests that this approach may not be effective for all patients (10–12) and strict rest beyond 48 h may in fact be detrimental to other patients (11, 12). Concurrently, there is evidence that more active and targeted treatment approaches may be beneficial to patients (11, 13, 14). In response to this evidence, researchers and clinicians have begun advocating for more active and targeted treatment approaches for treating the specific clinical profiles or subtypes of symptoms/impairment following mTBI (11, 14, 15).

Previous research on the effectiveness of treatments for mTBI has been limited in that only single treatments [e.g., (16)] have been used and/or multiple treatments have been applied across all patients groups without regard to specific symptoms and impairment or clinical profiles. In addition, when multiple treatments have been applied, separate treatment effects for each intervention were not considered [e.g., (17)]. The T-MD intervention in the current proposal will implement targeted interventions for seven affected domains including: (1) anxiety/mood, (2) cognitive, (3) migraine, (4) ocular, (5) vestibular, (6) sleep, and (7) autonomic. Each intervention will target a specific affected domain (e.g., vestibular rehabilitation for a patient with vestibular impairment and/or symptoms), but not all patients will receive all interventions. This approach better reflects precision clinical care models and may provide a more effective and efficient therapeutic pathway for patients with complex mTBI.

Research on the effectiveness of treatment following mTBI has yet to provide concomitant evidence of changes in the brain that may underly clinical findings. Functional near-infrared spectroscopy (fNIRS) is an optical imaging technique that measures temporal–spatial changes in oxygenated (activation) and deoxygenated (deactivation) hemoglobin concentrations in the cerebral cortex and is highly correlated with cerebral blood flow (CBF). Functional NIRS provides an objective measure of brain injury *via* changes in CBF that correspond to functional impairments in cognition (18) and vestibular function (19). Functional NIRS may provide an objective measure of treatment effectiveness by evaluating changes in brain activation at rest and during a cognitive paradigm in conjunction with clinical outcomes.

The overall objective of this multisite RCT is to determine the effectiveness of a T-MD intervention compared to usual care (behavioral management) in military-aged civilians with complex mTBI (anxiety/mood, cognitive, migraine, ocular, vestibular, sleep, and autonomic domains). The study involves three primary aims: (1) compare using an RCT the effectiveness of T-MD (anxiety/mood, cognitive, migraine, ocular, vestibular, sleep, autonomic domains) intervention to usual care (behavioral management) on improving clinical profile-based outcomes including symptoms, impairments, return to activity (RTA), and healthcare utilization costs in 200 military-aged civilian patients with complex mTBI; (2) to compare changes in brain activation (i.e., CBF) as measured by fNIRS in the T-MD and usual care intervention groups; and (3) to correlate changes in symptoms and impairment with brain activation as measured by fNIRS. We will also explore factors (e.g., demographics, medical history, injury information) that may influence the efficacy of T-MD on NSI, PGIC, and RTA outcomes.

## Methods and analysis

2.

### Study design

2.1.

A prospective, single-blinded, two-group multicenter RCT of T-MD versus usual care (i.e., behavioral regulation) in military-aged civilians with complex mTBI will be conducted at two concussion specialty clinics: (a) University of Pittsburgh Medical Center Sports Concussion Program (Pittsburgh, PA), and (b) Inova Sports Medicine Concussion Program (Fairfax, VA). The current study will employ a two-group repeated measures (baseline, 2-week, 4-week, 3-month) design with permuted block random assignment. The study will be conducted under approvals from University of Pittsburgh Institutional Review Board (IRB) and Human Research Protection Office (HRPO) IRBs. The University of Pittsburgh’s IRB will act as the single site IRB for this project.

### Allocation to study arms

2.2.

Participants will be screened and recruited from two concussion specialty clinics, and randomization will be stratified by site. Within site, a permuted block randomization with random block sizes with a 1:1 allocation ratio will be used. The lead biostatistician will generate the randomization list which will be uploaded into the electronic data capture system. The site coordinator will receive the allocation for each participant once all eligibility information is entered and the participant is deemed eligible for the trial. Participants will be randomized to either the T-MD or usual care intervention arm. Treating clinicians and study research staff will not be blinded to participant group, as they will be employing study procedures and supervising participants in the study. The Principal Investigators will be blinded to participant group assignment throughout the study, including during data analysis.

### Participants and eligibility criteria

2.3.

A total of 250 participants with complex mTBI will be enrolled into the study. We expect complete data for 200/250 (80%) participants per estimated combined attrition rates of 20%. A total of up to 125 participants will be enrolled at each site. Aside from age, the demographics of the sample of participants will not be controlled, as a convenience sample will be enrolled. Based on the combined population demographics of the Pittsburgh and Northern Virginia areas where the trial will occur, we expect participants to reflect closely the racial/ethnic representation from the 2013 Demographics Report of Active-Duty military (20). Specifically, we expect participants to have the following demographic characteristics: White (70%), African American (17%), and other minority (13%). However, given the higher numbers of women treated for concussion at the two sites, we expect the representation of women to be higher in the current study (e.g., 50–60%) compared to the US active-duty military population (e.g., 40%).

Inclusion criteria are age 18–49 years, normal/corrected vision, and diagnosed with a currently symptomatic mTBI with a clear mechanism of injury in the past 8 days-6 months. In addition, participants will have complex mTBI symptoms and/or impairments in at least one of the following domains: anxiety/mood, cognitive, migraine, ocular, vestibular, sleep, autonomic; per a comprehensive assessment, clinical exam/interview, and adjudication process. Exclusion criteria for this study include history of vestibular disorder (e.g., benign paroxysmal positional vertigo, unilateral or bilateral vestibular hypofunction), history of neurological/mental health disorders (e.g., epilepsy, seizure disorders, schizophrenia, bipolar), history of brain surgery/malformations/tumors, diagnosed with cardiac, peripheral or cerebrovascular disease, experienced chest pain or shortness of breath while at rest or with mild exertion, been told by a doctor to only conduct physical activity under medical supervision, previous moderate to severe TBI, <8 days- or > 6 months following current complex mTBI, currently pregnant or become pregnant during study, and/or currently involved in litigation associated with current or previous mTBI, currently on workman’s compensation, previously participated in the study, or previously received clinical concussion care at either participating site within the last 2 years. Participants with a history of mTBI, attention deficit hyperactivity disorder (ADHD), learning disability (LD), migraine, or motion sickness will not be excluded, which will more closely reflect the true characteristics of this population and increase the external validity of the study results.

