### Statistical analysis plan

2.6.

All data quality monitoring and analysis will be overseen by the lead biostatistician. Distributions of baseline characteristics for participants will be compared between T-MD and usual care intervention groups to assess effectiveness of the randomization. Statistical or clinical differences will be adjusted for in secondary analyses. All analyses for treatment group comparisons will use an intention-to-treat approach and results will be reported using the CONSORT extension to non-pharmacological randomized trials. The primary outcomes for this study are NSI (Aims 1, 3), PGIC scores (Aim 1) and brain activation as measured by fNIRS (Aims 2, 3). The NSI and PGIC will be measured at baseline, 2 weeks, 4 weeks, and 3 months post randomization. Brain activation will be measured at baseline and 4 weeks. NSI and fNIRS will be treated as continuous and PGIC scores will be dichotomized into minimal or no change vs. moderate or greater change. For Aim 1, we will analyze the NSI score using linear mixed models with fixed effects for site, intervention, time, and the intervention by time interaction along with a random effect for subject to control for the correlation within person over time. We will use a generalized linear mixed model with a logit link and the same fixed and random effects for the dichotomized PGIC outcome. We will test each intervention’s effect over time using the intervention*time interaction. For Aim 2, we will calculate change scores by subtracting the fNIRS value at 4 weeks from the baseline value. We will use a two-sample t-test to compare the change scores between the intervention and control group. For Aim 3, we will calculate change scores by subtracting the NSI value at 4 weeks from the baseline value. The efficacy of the intervention will be determined based on the results for each outcome and interpreted within the domain of that specific outcome with no adjustment for multiplicity. Pearson correlation will be used to examine the relationship of change in NSI to the fMRI value at 4 weeks in the intervention group.

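### Time since injury spans 8 days to 6 months and is plausibly prognostic, but the primary NSI model and the fNIRS t-test omit it, which gives up some precision at no saving

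*Protocol article*

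**What the plan says.** Section 2.3 of the protocol article requires a "clear mechanism of injury in the past 8 days-6 months" and excludes anyone outside that window, so the injury date must be known for every participant. Section 2.2 says that "randomization will be stratified by site" and names no other stratum.

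Section 2.6 fixes the three primary analyses:
- **NSI:** "linear mixed models with fixed effects for site, intervention, time, and the intervention by time interaction", plus a random subject effect. The test is the intervention-by-time interaction.
- **PGIC, dichotomized:** a "generalized linear mixed model with a logit link and the same fixed and random effects".
- **fNIRS:** "We will use a two-sample t-test to compare the change scores between the intervention and control group".

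Time since injury is in none of them. Two other provisions of Section 2.6 come close. Baseline characteristics are compared between arms, and statistical or clinical differences are adjusted for in secondary analyses. Injury information is also listed among the factors explored for NSI, PGIC and RTA, by estimating the intervention effect within levels of each factor at 4 weeks.

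On natural recovery, the Introduction says: "Although most military personnel with mTBI will recover in 3–4 weeks, many experience symptoms and impairments lasting months or longer".

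**The concern.** The eligibility window is wide: with 30-day months, 180 / 8 gives a 22.5-fold range. The intervention lasts 28 days. A patient enrolled on day 8 is followed to about day 36, across the 3 to 4 weeks (days 21 to 28) in which the Introduction expects most people with mTBI to recover. Allowing up to 7 days before the baseline assessment (Section 2.5) moves this to about days 15 to 43, which still covers that period. A patient enrolled at 5 months is well past it. It is therefore plausible that the two differ in expected change whatever their arm.

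Change by arm is what the NSI interaction test and the fNIRS t-test examine. Any part of that change predicted by time since injury stays in the error term if the variable is left out. At stake is precision that could be had from a value already on file. The article does not simply leave the matter open: it lists the model terms, names the fNIRS test, and assigns baseline adjustment to secondary analyses.

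**Working it through.** **Inputs from Section 2.6:** difference 5 NSI points, SD 14, 100 analysed per arm, four measures, AR(1) correlation 0.7, two-sided alpha 0.05, stated power 80%. For fNIRS: effect size 0.5, 100 per arm, stated power 94%.

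**Assumed, because the article does not give it:** R², the share of variance in change explained by time since injury, taken as 0.02 to 0.20. It is assumed equal for all contrasts with baseline.

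**1. Reproduce the stated NSI power.** The article gives no pattern of effects over visits. I used a difference of 0 at baseline and 5 at each later visit, δ = 5u with u = (0, 1, 1, 1). The variance of an arm difference at one visit is 14² × 2/100 = 3.92. With R the AR(1) correlation matrix and 1 − 0.7² = 0.51:
- u'R⁻¹u = (1.49 + 1.49 + 1 − 2.8)/0.51 = 2.314
- 1'R⁻¹u = (0.09 + 0.09 + 0.30)/0.51 = 0.941
- 1'R⁻¹1 = 0.78/0.51 = 1.529
- Noncentrality λ = (25/3.92) × (2.314 − 0.941²/1.529) = 6.378 × 1.7345 = 11.06

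A 3-df chi-square test with λ = 11.06 has power 80.6% (79.8% to 80.3% with F reference distributions). This agrees with the stated 80%.

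**2. NSI with the covariate and its visit interaction.** The residual variance of change is multiplied by (1 − R²), so λ becomes 11.06/(1 − R²). The last column is the number analysed that would keep the power at 80.6%, 200 × (1 − R²).

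| Assumed R² | Power | N for unchanged power |
|---|---|---|
| 0 | 80.6% | 200 |
| 0.02 | 81.5% | 196 |
| 0.05 | 82.8% | 190 |
| 0.10 | 85.0% | 180 |
| 0.20 | 89.2% | 160 |

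**3. Does a main effect suffice?** No. The planned test is within-subject, and a covariate that shifts all visits equally cancels from it. A mixed-model simulation (150 replicates per scenario) gave these model standard errors for the intervention-by-4-week term:

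| Covariate acts on | No covariate | Main effect only | With visit interaction |
|---|---|---|---|
| Level only | 1.833 | 1.833 | 1.837 |
| Change | 1.883 | 1.883 | 1.837 |

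The first row shows the small cost when the covariate does not predict change. In the second row the covariate explains about 9% of the change to 4 weeks: 4.5² = 20.25 against 2 × 196 × (1 − 0.49) = 199.9, and 20.25/220.2 = 0.092.

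**4. fNIRS.** Power ≈ Φ(0.5 × √50/√(1 − R²) − 1.96). At R² = 0 this is Φ(3.536 − 1.96) = 94.2%, in line with the stated 94%. At R² = 0.05, 0.10 and 0.20 it is 95.2%, 96.1% and 97.7%.

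**The case against.** The strongest reply is that no part of the article relates days since injury to NSI or fNIRS change in this sample. The statement that "most military personnel with mTBI will recover in 3–4 weeks" concerns mTBI in general, whereas the trial takes only patients who are still symptomatic with complex mTBI. This stands as a limit on size: R² is unknown, and at 0.02 the gain is under one percentage point. It does not remove the plausibility, because Section 2.4.2 defines complex mTBI by impairments lasting more than a week, which is short of the 3 to 4 week recovery time.

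Four stronger readings are tempting, and the document does not support them.

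- **The trial is underpowered.** A single-visit comparison has SE 14 × √(2/100) = 1.98 and power Φ(5/1.98 − 1.96) = 71.4%. That is not the planned test. The planned interaction test reproduces the stated 80%.
- **The comparison is biased, or imbalance is ignored.** Randomization protects the comparison, and observed baseline differences are to be adjusted for in secondary analyses. What remains is that this adjustment depends on the data seen and leaves the primary result as it is. The exploratory estimates within levels add no precision to the primary test either.
- **Time since injury should have been a stratum.** Covariate adjustment gives the precision without any change to the allocation scheme.
- **The same argument carries over to PGIC and RTA.** In a logistic model, adjustment changes the odds ratio to a conditional one, so a gain in precision does not transfer directly. The article states no RTA model to amend.

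**Conclusion.** The point holds as a missed efficiency. Section 2.6 fixes primary analyses that leave out a variable known for every participant and plausibly related to the change being tested. The tests are valid and the sample size is not in error.

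For assumed R² between 0.02 and 0.20, the gain in NSI power runs from about 1 to 9 percentage points (80.6% to between 81.5% and 89.2%). The fNIRS gain is about 1 to 3.5 points for R² between 0.05 and 0.20. These figures rest on the assumed R², on a constant 5-point effect at all visits after baseline, and on the article's own SD and AR(1) correlation. If time since injury is only weakly prognostic in this selected sample, the gain will be near the bottom of the range. The change is worth making because it costs little, not because the trial depends on it.

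**What to change.** Before any outcome is compared by arm, amend Section 2.6 as follows:
- **NSI:** add log(days from injury to randomization) and its interaction with visit as fixed effects in the primary model. The interaction is essential, since the main effect alone does nothing for the planned test.
- **fNIRS:** replace the two-sample t-test by a linear model of change on intervention and log days since injury.
- **PGIC:** adding the terms is optional. If they are added, state that the odds ratio is conditional on time since injury.

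Leave randomization unchanged.

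The cost is a sentence or two of text and a few degrees of freedom: four parameters in the NSI model (one main effect and three visit interactions) and one in the fNIRS model. No additional patients or data are required. The log form is a modelling choice and should be fixed in advance with the rest.

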### Measures and instrumentation

2.4.

#### mTBI diagnosis criteria

2.4.1.

Diagnosis of mTBI will be operationally defined in line with current U.S. military assessments as including the following diagnostic criteria: clear mechanism of injury; Glasgow Coma Scale (GCS) = 13–15; reported or observed signs (e.g., loss of consciousness, amnesia, disorientation/confusion) at time of injury; and/or current reported symptoms (e.g., headache, dizziness, nausea) and/or impairments (e.g., cognitive, balance, visual).

#### Complex mTBI diagnosis criteria

2.4.2.

The complex mTBI diagnosis will be defined as persistent mTBI symptoms that are associated with observable clinical impairments lasting more than a week following injury. The domains and assessments that will be used to screen for complex mTBI are documented in Table 1 below. Participants must demonstrate a positive finding in at least one of the complex mTBI domains to be considered for enrollment into the study. Tests from the NIH Common Data Elements (CDE) (21) set for sport-related concussion will be utilized when available.

**Table 1 tab1:** Assessments for determining complex mTBI domains.

Domain	Positive findings/indication for enrollment
Anxiety/Mood	Global Severity Index (GSI) T-score > 50; or CP-Screen Anxiety(A)/Mood(M) Avg score ≥ 2 or 1+ individual item = 3 BSI-18 subscale T score ≥ 63 (Overall, A, M) **Subdomains**: Anxiety (A):  Mood (M):  Both (M/A): 
Cognitive	≤7^th^% on one or more ImPACT composite scores; or CP Screen Cognitive Avg score ≥ 2 or 1+ individual item = 3; AND ≤ 30 on ImPACT Impulse Control; AND < 9 on REY 15
Migraine/ Headache	≥2 on ID Migraine- migraine (M); or ≥ Grade 2 (≥ 50) on HIT-6- headache (HA); or CP-Screen Migraine Avg score ≥ 2 or 1+ individual item = 3 **Subdomains**: Headache (HA) Only:  Both (M/HA):  Migraine (M) with ocular/light sensitivity:  Migraine (M) with noise sensitivity:  Migraine (M) with motion sensitivity: 
Ocular	≥2 on smooth pursuits or hor/ver saccades, or near point convergence (NPC) ≥10 cm; or CP-Screen Ocular Avg score ≥ 2 or 1+ individual item = 3
Vestibular	≥2 on vestibulo-ocular reflex (VOR) and/or visual motion sensitivity (VMS); or > 9 total errors on mBESS; or CP-Screen Vestibular Avg score ≥ 2 or 1+ individual item = 3
Sleep	≥5 on PSQI global score, or CP-Screen Sleep Avg score ≥ 2 or 1+ individual item = 3
Autonomic	Increase of 3+ (from resting value) on VAS; or Unable to complete BCBT per patient or clinician

Clinical Profiles Screen (CP-Screen), Brief Symptom Inventory-18 (BSI-18), Immediate Post-Concussion Assessment and Cognitive Testing (ImPACT), REY15-Item Memorization Test (REY 15), Headache Impact Test-6 (HIT-6), Pittsburgh Sleep Quality Index (PSQI), Visual Analogue Scale (VAS), Buffalo Concussion Bike Test (BCBT).

